#### Additional sensitivity analyses

In accordance with the APOSTEL 8 trial, the following subgroup analyses are planned:

Singleton and multiple pregnancy separately.Cervical length <15 mm vs cervical length 15–30 mm and a positive fibronectin test (or no

cervical length measurement and a positive fibronectin test or Partus test).

Ruptured vs intact membranes at entry.Previous preterm birth.Excluding children that exceed the optimal window of 3;9 years–4;3 years of corrected age. In sensitivity analyses, we will use imputation techniques to impute missing outcome data for children lost to follow-up. Multiple imputation techniques will only be applied when it can be assumed that data are missing at random and the follow rate is >70%. the follow-up rate is lower than 70, a best-case and worst-case scenario analyses will be performed.Composite outcome of deceased children or survived children with abnormal cognitive and/or behaviour development. Combining mortality data with survival of children with a severe developmental disability will help in providing the full scope of relevant outcomes from the start of randomisation until up to 4 years of age. The denominator in this analyses will be all children born in the APOSTEL 8 trial, instead of the number of children included in follow-up. However, this outcome has some challenges due to the high probability of loss to follow-up (as is the case in many obstetrical follow-up studies after several years), and therefore, the inevitable need to deal with missing data. This will be done by either applying multiple imputation techniques or, in case of a high loss to follow-up, a worst-case and best-case scenario analyses.

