## Methods and analysis

### Study setting

This study will be a follow-up study of the APOSTEL 8 study, an international, multicentre, randomised, double-blinded, placebo-controlled trial performed across 30 hospitals situated in the Netherlands, UK and Ireland (NL61439.018.17, EudraCT-number 2017-001007-72). The APOSTEL 8 trial includes women with threatened preterm birth between 30 and 34 weeks of gestation. Threatened preterm birth is defined as uterine contractions with (1) a cervical length <15 mm; (2) a cervical length of 15–30 mm with a positive fetal fibronectin test; or (3) a positive fibronectin test or insulin-like growth factor binding protein-1 (Actim-Partus test) in centres where cervical length measurement is not part of local protocol or (4) ruptured membranes. Eligible women are randomised to atosiban or placebo (0.9% saline) for 48 hours. The primary outcome is a composite of adverse perinatal outcomes including perinatal mortality and six severe perinatal morbidities: bronchopulmonary, periventricular leukomalacia >grade 1, intraventricular haemorrhage >grade 2, necrotising enterocolitis ≥stage 2, retinopathy of prematurity >grade 2 or needing laser therapy, andculture-proven sepsis. Secondary outcomes include various infant and maternal outcomes which can be found in the published protocol. The APOSTEL 8 started in 2017 and complete recruitment in 2023. Long-term follow-up of the APOSTEL 8 study was announced in the original trial protocol.^13^ This long-term follow-up study is directed at the children born to mothers who participated in the APOSTEL 8 trial, therefore, either exposed to atosiban or placebo during pregnancy. We will use four parent-reported questionnaires to assess neurodevelopment, behaviour problems and general health. Data collected in the original trial will be linked to the data obtained in this follow-up study. The study protocol has been developed according to the Standard Protocol Items: Recommendations for Interventional Trials criteria.

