### Participants/eligibility criteria

Children of both singleton and multiple pregnancies, born to mothers who participated in the APOSTEL 8 trial, will be eligible for inclusion. Assessment will be performed when children are around 4 years of corrected age (ideally between 3 years and 9 months (3;9) to 4 years and 3 months (4;3) years of corrected age). Participants who did not give consent to be approached for follow-up research in the original APOSTEL 8 trial, will not be approached in this follow-up study. Also, participants included in the UK or Ireland will not be eligible for inclusion.

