#### Statistical analysis

Differences in baseline characteristics of APOSTEL 8 follow-up participants will be compared between atosiban and placebo group using unpaired t-test, Mann-Whitney U test, χ^2^ test or Fisher’s exact test when appropriate. A two‐sided p<0.05 will be considered statistically significant. To detect potential attrition bias, baseline characteristics of follow-up participants will be compared with those lost to follow-up.

For the main outcomes, neurodevelopment and behaviour, we will report mean scores with SD and dichotomous outcomes (abnormal/mildly abnormal) of the domains and total score of the ASQ-3, Vineland screener and SDQ. For general health-related outcomes, we will report on the outcomes as previously described. For the outcome mortality, the denominator needs to be changed into all children born to participants of the original APOSTEL 8 trial.

For the main analysis, all outcomes will be analysed using generalised linear mixed effects model to enable accounting for the dependence of multiple pregnancies. For continuous outcomes, this will provide mean difference with 95% CI and for dichotomous outcomes OR with 95% CI. All analyses will be performed according to the intention-to-treat principle and complete case analysis using SPSS or R (latest version).

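### Analysing singletons and multiples separately does not estimate whether the effect differs, and the cervical-length subgroup mixes women of unknown length into the 15–30 mm level

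*Protocol article*

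**What the plan says.** Under Additional sensitivity analyses, the protocol article introduces the list with "In accordance with the APOSTEL 8 trial, the following subgroup analyses are planned". Four factors follow:

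- Plurality: "Singleton and multiple pregnancy separately".
- Cervical length: "Cervical length <15 mm vs cervical length 15–30 mm and a positive fibronectin test (or no", continued on the next line as "cervical length measurement and a positive fibronectin test or Partus test". Women who were never measured therefore share a level with those measured at 15–30 mm.
- Membrane status and obstetric history: "Ruptured vs intact membranes at entry.Previous preterm birth".

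Study setting explains who the unmeasured women are. They qualified on a biochemical test alone "in centres where cervical length measurement is not part of local protocol". Participants/eligibility criteria adds that "participants included in the UK or Ireland will not be eligible for inclusion". The number of unmeasured women who remain is not given.

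Statistical analysis specifies a generalised linear mixed model for all outcomes, giving mean differences or odds ratios with 95% CIs. It names no treatment-by-subgroup term and excludes none.

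**The concern.** A subgroup analysis asks whether the treatment effect differs between levels. For plurality, the text fixes two stratified analyses, and these do not answer that question. One group can cross the significance threshold and the other miss it simply because one is larger. If the paper then reported an effect in singletons but not in multiples, it could suggest a difference that the data do not show.

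The cervical factor has a different problem. Unmeasured women have an unknown length, so any of them under 15 mm sit in the wrong level for a length contrast. Membership of the second level also depends partly on centre practice. A real difference in effect by cervical length would look smaller than it is.

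**Working it through.** **Inputs from the document (Sample size).** About 635 singleton and 125 multiple pregnancies; 200 children per arm; two-sided Z-test with pooled variance at 0.05; 80% power for a 12-point difference.

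**Assumptions.** Two children per multiple pregnancy; equal follow-up in both groups; event rates of 30% vs 18%. The article states no control rate. The clustering of siblings is ignored.

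**Step 1. The plan's own power figure.** Power = Φ[(d − 1.96·SE₀)/SE₁] (the opposite tail is negligible), where SE₀ = √(2·p̄(1−p̄)/n) and SE₁ = √([p₁(1−p₁)+p₂(1−p₂)]/n). With 30% vs 18% and n = 200, SE₀ = 0.0427 and SE₁ = 0.0423, so power is 80.5%. The assumed rates agree with the stated 80%. At 38% vs 26%, power is 73.2%.

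**Step 2. Group sizes.** Children: 635 + 2×125 = 885. Of 400 followed up, 400×635/885 = 287 are singletons and 400×250/885 = 113 come from multiples, or about 143.5 and 56.5 per arm.

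**Step 3. The same true effect in both groups (30% vs 18%).**

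| Group | n per arm | SE₀ | SE₁ | Power |
|---|---|---|---|---|
| Singletons | 143.5 | 0.0504 | 0.0499 | 66% |
| Multiples | 56.5 | 0.0804 | 0.0796 | 32% |

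- Exactly one significant: 0.664×0.681 + 0.319×0.336 = 0.56.
- Both significant: 0.664×0.319 = 0.21.

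At 38% vs 26%, power is 59% and 28%, and exactly one group is significant in 54% of trials. At those rates, the figure is 49% for equal halves and 60% for a 167:33 split per arm. With no effect at all, it is 2×0.05×0.95 = 9.5% per factor.

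Allowing for sibling correlation would lower power in multiples. With singleton power above one half, that moves the 56% slightly upward.

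**Step 4. What an interaction test could show.** On the risk-difference scale, SE = √(2·p(1−p)·(1/n₁+1/n₂)). At a mean rate of 32%:

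| Split per arm | SE | Power for a 12-point difference in effect | Difference detectable with 80% power (2.8×SE) |
|---|---|---|---|
| 143.5 : 56.5 | 0.104 | 21% | 29 points |
| 100 : 100 | 0.093 | 25% | 26 points |

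At the 24% mean rate of the 30% vs 18% case, the plurality split gives SE = √(2×0.24×0.76×(1/143.5+1/56.5)) = 0.095 and power of about 24%, so the picture is the same.

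**Step 5. Cervical contrast.** Let s be the unmeasured share of the pooled level and q the share of those truly under 15 mm. If the effect depends on true length, and the other unmeasured women resemble the 15–30 mm group, the pooled level's effect is a mixture and the contrast shrinks by s×q:

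| s | q | Shrinkage |
|---|---|---|
| 10% | 30% | 3% |
| 30% | 50% | 15% |
| 50% | 70% | 35% |

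Neither s nor q is in the document.

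**The case against.** The strongest objection is that the article does not reject interaction tests. Only plurality carries the word for separate analysis. Cervical length and membranes are written as contrasts, and previous preterm birth has no comparator. A reader might infer that all four factors will be analysed by level instead of by interaction, but the text does not support that. Such a term may also stand in the parent trial's protocol or an analysis plan that is not shown. This stands, and it limits the first part of the point to plurality.

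A reader might also infer that each level will be judged at p<0.05. The sentence "A two‐sided p<0.05 will be considered statistically significant" sits in the paragraph on baseline characteristics and attrition, and outcomes are to be given as estimates with 95% CIs. No rule treats one significant and one non-significant level as a subgroup difference. It would therefore go too far to say that subgroup claims will often be false.

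Nor is multiplicity a strong argument here. Treating tests as independent, the chance of at least one false positive under no effect is 1 − 0.95⁸ = 33.7% for eight level-wise tests and 1 − 0.95⁴ = 18.5% for four interaction tests. Interaction tests reduce the problem only in part.

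On cervical length, the second level is openly described and can be read as women who qualified by a biochemical test, so it is not mislabelled. This also stands. As a contrast of cervical length, however, it remains mixed. With UK and Irish participants excluded, few unmeasured women may be left and the dilution may be negligible.

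**Conclusion.** The point holds in a limited form. As written, the plurality analysis gives two effects and no estimate of their difference. The 56% figure rests on the assumed 30% vs 18% rates, two children per multiple pregnancy and no clustering; across the other rates and splits examined it is about 49% to 60%. It describes how often significance would disagree between groups, not how often the investigators would draw a wrong conclusion.

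The cervical grouping biases a length contrast toward zero if any unmeasured woman is under 15 mm and the effect varies with length. The 3% to 35% range comes wholly from assumed s and q. Both matters concern additional analyses, so this is a minor improvement.

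**What to change.** For plurality, and for the other listed factors, add a treatment-by-subgroup term to the mixed model already planned. Report the interaction estimate with its 95% CI, give the level-specific estimates with CIs as exploratory, and make no significance claims by level. Report women with no cervical measurement as their own level, or leave them out of the contrast between under 15 mm and 15–30 mm.

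The cost is a few words and one model term per factor. There are two downsides. The interaction estimates will be imprecise, so a non-significant interaction must not be read as evidence of equal effects. The measured 15–30 mm level also becomes smaller. The abstract says that the protocol is published before the results are analysed, so the change can be recorded in advance.

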#### Data management

To ensure confidentiality, participants of the original APOSTEL 8 trial will be registered pseudonymised using a six-digit subject identification code. Only if necessary, researchers are able to identify subjects by a code. Procedures of this follow-up study will all be in accordance with the Dutch Personal Data Protection Act. Questionnaire will be collected using the data management system Castor Electronic Data Capture. For this data collection, the subject identification code will be used.

#### Patient and public involvement

Late neurodevelopmental morbidity is one of the core outcomes identified in the core outcome set for studies evaluating interventions to prevent preterm birth.^37^ During the development of this core outcome set, patient representatives, members of patient organisations (eg, the European Foundation for the Care of Newborn Infants) and parents were actively involved. Furthermore, members of the Parents of Preterm Children Association (care4neo.nl) have stressed the importance of follow-up research. In 2017, 75 of their members filled in an online survey wherein 85% of the parents expressed to have concerns about their child’s long-term development. In their opinion, crucial outcomes to assess in long-term follow-up research are; child’s school attainment, cognitive development, behaviour and psychological problems, motor skills, respiratory problems, general health, growth and medication use. In 2019, our research team organised a focus group for women who delivered preterm, showing comparable results. Both the online survey and focus group have primarily determined our choice of outcomes in this follow-up study.

Two Dutch patient associations, the Vereniging van Ouders van Couveusekinderen (freely translated to Society of parents of children admitted to NICU) and the Nederlandse Vereniging van Ouders van Meerlingen (freely translated to Dutch society of parents of multiples) were involved in the design of the original APOSTEL 8 trial and will be updated on progress of the study and informed of study results.
